### Adherence to the interventional program

The employment specialists and the IPS team leaders will assess the use of IPS services, including content and number of contacts between employment specialist and participants. The cognitive specialists will register adherence to the cognitive remediation and social skill groups, including group session attendance and whether home work is completed. In the control group, all contact between the participants and the social worker or vocational counselor will be assessed. It will also be possible to assess whether the controls are allocated to a vocational rehabilitation program of any kind and the duration and content of the rehabilitation. These data will be obtained from the DREAM register and from records in the job centers.

### Sample size and power calculation

No previous IPS trials or similar studies have been conducted in Denmark that could contribute to an estimation of the expected average number of hours of work among participants in the IPS intervention. A European IPS multicenter trial found a difference between the IPS group and the control group (vocational services) of 150 h in competitive employment in an 18-month follow-up period, and standard deviation was 500 [19]. A difference of 150 h in competitive employment or education is considered clinically relevant. If the outcome within each intervention group is normally distributed with a standard deviation on 500 and with a true mean difference of 150 between the intervention and the control group, the present trial will need 250 participants in both intervention arms and additionally 250 control participants to be able to reject the null hypothesis that the population means of the experimental and control groups are equal with probability (power) of 80 %. The type I error probability associated with the null hypothesis is 1.25 %. A type I error of 1.25 % was chosen to give the possibility to make four comparisons: (1) IPS versus service as usual, (2) IPS versus IPS enhanced, (3) IPS enhanced versus service as usual, and (4) IPS + IPS enhanced versus service as usual. If we encounter difficulties in recruiting 250 participants to each group, we will exclude comparison (4) as a primary comparison. With three primary comparisons, we use a type I error of 1.67 % in the sample size calculation, accumulating a sample size of 236 patients in each group. Power calculations on calculations of the secondary outcome measures were carried out (Table 5) and indicate that a sample size of 250 patients per group would be adequate to detect relevant significant differences.

**Table 5 Tab5:** Power calculation

Outcome measure	δ expected difference in mean	σ expected standard deviation	α	Power	Reference
Days to first employment or beginning of education	68	45	0.0125	1.000 (*t* test)	Bond et al. [8] (2008),
Cognitive function	0.3	0.7	0.0125	0.989 (*t* test)	McGurk et al. [13] (2005)
The Brief Assessment of Cognition in Schizophrenia [32]					
Function measured with Personal and Social Performance (PSP) scale [31]	7	14	0.0125	0.999 (*t* test)	Kawata et al. [31] (2008). Nasrallah et al. [46] (2008) (No IPS studies use PSP scale. δ is estimated)
Self-efficacy measured with General Self-Efficacy scale [37]	0.28	0.85	0.0125	0.880 (*t* test)	Tsang et al. [14] (2010)
Self-esteem measured with the Rosenberg Self-Esteem scale [38]	0.3	0.55	0.0125	0.992 (*t* test)	Mueser et al. [47] (2004), Howard et al. [18] (2010), Drake et al. [48] (1999). None of the studies shows difference in mean. σ is between 0.55 and 0.68.
Competitive employment or education during follow-up period	50 % vs. 34 %	-	0.0125	0.807 (chi-squared test)	Bond et al. [8] (2008)
Dichotomous yes/no					

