### Data analysis plan

The main null hypothesis to be tested is that there is no difference between the three groups in hours in competitive employment or education in the 18-month follow-up period. All randomized participants will be analyzed, including those who stop receiving treatment, according to the intention-to-treat principle. All continuous outcome measures, including the primary outcome “hours in competitive employment or education”, will be analyzed by using generalized linear models. In situations in which the continuous measure is non-normally distributed, a non-parametric model will be used. Multiple imputations will be used to impute a distribution of missing values. Furthermore, linear mixed models with repeated measurements and unstructured covariance matrixes will be used to assess the potential interaction between time and intervention. The dichotomous secondary outcome “work or education at some point during the follow-up period” will be analyzed by using logistic regression. The secondary outcome “time-to-employment or education” will be analyzed by using the Cox proportional hazards model. All models will be adjusted for the stratification variables.

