## Discussion

This is the first trial investigating the effects of IPS in Denmark and will be one of the largest randomized trials investigating IPS to date. As a comparison, 14 trials included in a Cochrane review showed a median sample size per arm of 70 participants and a range of between 20 and 156 [11]. Furthermore, this trial will be the first large-scale trial, with a long follow-up period, enhancing the IPS intervention with both cognitive remediation and social skills training. The design of the trial has several strengths. Firstly, a sample size calculation was made according to the primary outcome, hours in competitive employment or education. The power is estimated for all secondary outcome measures, showing that a sample size of 750 participants is sufficient to show a relevant effect size with a power above 80 %. Secondly, the risk of selection bias related to allocation sequence generation and concealment is limited, as the Copenhagen Trial Unit performs a central web-based randomization according to a computer-generated allocation sequence. Thirdly, assessors are blinded, and blinding will be used wherever possible to prevent bias. Data will be analyzed according to the intention-to-treat principle, which together with an intense follow-up of patients should limit the risk of attrition bias. Finally, internal validity is addressed by implementing fidelity ratings. The fidelity ratings have high priority and will be conducted throughout the trial period to ensure that evidence-based practice is adhered to.

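### Table 5's power of 1.000 for days to first employment or education comes from a t test on complete start times and is not the power of the planned Cox analysis

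*Protocol article*

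**What the plan says.** All places are in the protocol article.

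- **Table 5 (Sample size and power calculation)** gives for this outcome: "Days to first employment or beginning of education 68 45 0.0125 1.000 (*t* test". The columns are expected difference, standard deviation, alpha and power. The text introducing the table reads it at 250 per arm: "a sample size of 250 patients per group would be adequate to detect relevant significant differences".
- **Table 5, last outcome** gives the expected share with any start: "Competitive employment or education during follow-up period 50 % vs. 34" per cent. The arms are not labelled.
- **Alpha**: "A type I error of 1.25 % was chosen to give the possibility to make four comparisons".
- **Data analysis plan**: "The secondary outcome “time-to-employment or education” will be analyzed by using the Cox proportional hazards model". All randomized participants are analyzed by intention to treat, and the main null hypothesis in the same section sets the window: "no difference between the three groups in hours in competitive employment or education in the 18-month follow-up period".
- **Use made of the table**: the Outcome and assessments section restricts secondary outcomes to those with at least 80 % power, and the Discussion lists as a strength: "The power is estimated for all secondary outcome measures, showing that a sample size of 750 participants is sufficient".

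The power section gives no hazard ratio, event count or censoring assumption for this outcome.

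**The concern.** The two rows of Table 5 describe the same participants over the same follow-up, and they do not fit together. The first treats days to start as a number known for all 250 people in each arm. The second says that half of one arm and two thirds of the other never start, so their days are censored at 18 months. A mean over whole arms cannot be computed from such data, and the plan does not intend to compute one, since it specifies a Cox model. The power of that model depends on the number of events and the hazard ratio, neither of which enters the printed calculation.

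At stake is whether this outcome has been shown to meet the plan's own criterion for secondary status, and whether the power reported for it is correct. This is a mismatch between the power method and the analysis method, not an arithmetic slip.

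**Working it through.** **Inputs.** From Table 5: difference 68 days, SD 45 days, alpha 0.0125, and 50 % versus 34 % starting. From the text: 250 per arm and 18 months (about 548 days). Assumed because not stated: two-sided testing, 50 % as the experimental arm and 34 % as control, and no censoring before 18 months.

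**1. The plan's own figure.** Standardized difference = 68/45 = 1.51. The test statistic is centred at 1.51 × √(250/2) = 16.9 against a critical value of 2.498. Power = 1.000, as printed. It is also 1.000 if one-sided or with 236 per arm.

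**2. How many people have a start day.**
- With one: 250 × 0.50 + 250 × 0.34 = 125 + 85 = 210.
- Without one: 125 (50 %) + 165 (66 %) = 290 of 500.

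**3. Whether 68 and 45 can describe whole arms.** Suppose times are normal with SD 45 in both arms.
- 50 % and 34 % started by a common cut-off implies a difference of (0 + 0.412) × 45 = about 19 days, not 68.
- A difference of 68 days with 50 % started in one arm implies Φ(−68/45) = about 6.5 % started in the other, not 34 %.

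On that model the two rows agree only if 68 and 45 describe people who started. A t test on starters alone (125 versus 85) also gives 1.000, but it compares subgroups selected after randomization, not all randomized participants.

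**4. Power of the planned analysis from the event rates.** Under proportional hazards:
- Hazard ratio = ln(0.50)/ln(0.66) = 1.668.
- Events = 250 × (0.50 + 0.34) = 210.
- Schoenfeld: Φ(√210/2 × ln 1.668 − 2.498) = Φ(1.21) = 0.887.
- Freedman: Φ(√210 × 0.668/2.668 − 2.498) = Φ(1.13) = 0.871.
- Simulated log-rank test, censoring at 548 days, 10,000 runs each: 0.879 (exponential times), 0.884 and 0.882 (Weibull, shapes 0.7 and 1.5).

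**5. Adding the timing input.** Let 50 % versus 34 % start, with starters' times normal, SD 45 and means 68 days apart. The absolute start days are not in the document. With assumed experimental means of 150, 200 and 300 days, simulated log-rank power is 0.994, 0.993 and 0.995.

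**6. Margin to the 80 % threshold.**
- At hazard ratio 1.668, 80 % power needs 171 events (Schoenfeld) or 178 (Freedman); 210 are expected.
- With the fallback of 236 per arm at alpha 0.0125, Schoenfeld power is 0.865.
- At 210 events, 80 % power needs a hazard ratio of exp[(2.498 + 0.842)/(√210/2)] = about 1.59. A power that rounds to 1.000 needs about 2.2.

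**The case against.** The strongest reply is that nothing in the plan turns on the difference. The outcome exceeds 80 % power on the event-based calculation too, so its rank, the sample size, the analysis and the Discussion's claim of power above 80 % are unchanged. The outcome does not drive the sample size, and the table openly labels the figure as a t test. All of this stands, and it limits the weight of the point.

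A second reply is that 0.89 is itself a partial answer, because it uses the event rates and discards the timing. If 68 and 45 days describe starters, the plan assumes both more starts and earlier starts, and power is about 0.99. This also stands. The range 0.87 to 0.89 holds under proportional hazards with the rates alone and should not be written in as the only correct value.

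A reader might go further and infer that the outcome is underpowered, or that a real effect could easily be missed. The document does not support that on its own inputs. One can lower the power by assuming a smaller difference in start rates, but that lowers the power of any test and does not measure the mismatch between t test and Cox model. A reader might also infer that a null result would be taken as proof of no effect. The protocol contains no rule for reading a null secondary result from its pre-trial power, so that consequence has no basis in the text.

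These replies do not rescue the printed row. Condensation into an article does not explain it either: both the t-test power and the Cox analysis are printed, and they disagree.

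**Conclusion.** The row is wrong as written. Power of 1.000 is correct for a t test on 250 observed times per arm, but on the plan's own rates 50 % and 66 % of the arms have no such time by 18 months, and the planned analysis is a Cox model on everyone randomized.

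The overstatement is modest: 1.000 against about 0.87 to 0.89 from the start rates alone, or about 0.99 with the timing difference added. Both values rest on Table 5's 50 % versus 34 %, on two-sided testing and on no earlier censoring; the first also assumes proportional hazards, and the second assumes normal start times among starters. Both exceed 80 %, so the outcome remains a legitimate secondary outcome.

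The mismatch itself is certain. The replacement figure depends on assumptions, since the protocol states no hazard ratio. No expected difference is given for enhanced IPS versus IPS, so the power of that comparison cannot be checked.

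**What to change.** Replace the t-test row for this outcome in Table 5 with an event-based calculation (Cox or log-rank) and print its assumptions:

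- 50 % versus 34 % with an event by 18 months, arms labelled, others censored at 18 months;
- about 210 events per pairwise comparison at 250 per arm;
- two-sided alpha 0.0125;
- hazard ratio about 1.67 if hazards are proportional;
- power about 0.87 to 0.89.

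If the authors want to keep the 68-day difference and SD 45, they should say that these describe starters only, state the assumed start times, and report the resulting power (about 0.99) as a second scenario. The outcome stays secondary, and the Discussion's statement of power above 80 % can stay.

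The cost is one table row and a short note on assumptions. The printed figure becomes somewhat less favourable. Sample size, data collection and the planned analysis do not change.

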	Obtained through interview	Cognitive function measured with the Brief Assessment of Cognition in Schizophrenia [32] (BACS)	X	X
	Obtained through interview	Function measured with Personal and Social Performance (PSP) Scale [31]	X	X
	Self-reported questionnaire	Self-efficacy measured with General Self-Efficacy (GSE) scale [37]	X	X
	Self-reported questionnaire	Self-esteem measured with the Rosenberg Self-Esteem scale [38]	X	X

To avoid the risk of multiplicity and type I errors, we will limit our secondary outcomes to outcomes with at least 80 % power. Other outcomes are considered “exploratory” when drawing conclusions. This means that we will consider any statistically significant result in any of these outcomes as exploratory or hypothesis-generating. This is because we have no sample size estimation for these outcomes, and thus the risk of an early false positive is increased; it is further increased because of the risk of multiplicity as a result of too many outcomes.

Exploratory outcomes cover the 30 and 60 months of register follow-up along with additional vocational measures that will provide a more nuanced picture of vocational status, including average monthly earnings and hours of work per week among those who obtain competitive employment. Furthermore, a range of non-vocational outcomes such as client satisfaction, health-related quality of life, empowerment, recovery, and substance abuse will be used to address other important factors hypothesized to influence the participants. Psychopathology will be measured to ensure no adverse effects of the intervention.

All exploratory and safety measures and the assessment instruments used are outlined in Tables 3 and 4. Trained and certified research assistants will perform all assessments. Inter-rater reliability tests will be performed prior to the trial and at least quarterly throughout the assessment period on the following instruments: Scale for the Assessment of Negative Symptoms [35], Scale for the Assessment of Positive Symptoms [35], PSP scale [31], and Hamilton Depression Scale (HAM-D6) [36]. The aim is to achieve an interclass correlation coefficient of more than 0.7. Consensus ratings will be performed on the remaining instruments.

**Table 3 Tab3:** Explorative measures and data collection

Outcomes	Source of collection	Assessment	Baseline	18-month follow-up	30 + 60-month register follow-up

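### Table 5 prints power 0.807 for competitive employment or education (yes/no), but its own inputs (50 % vs 34 %, alpha 0.0125, 250 per group) give 0.873

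*Protocol article*

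**What the plan says.** The section on sample size and power calculation sets the significance level: "The type I error probability associated with the null hypothesis is 1.25" per cent. It gives the reason: "A type I error of 1.25 % was chosen to give the possibility to make four comparisons". It then refers to Table 5 for the secondary outcomes and concludes that "a sample size of 250 patients per group would be adequate to detect relevant significant differences".

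The last row of Table 5 covers competitive employment or education during follow-up, yes or no. It gives 50 % vs 34 %, alpha 0.0125 and power "0.807 (chi-squared test").

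The self-esteem row lists difference, SD and alpha as "0.3 0.55 0.0125", with power 0.992 from a t test. Its reference note says of the cited studies that "None of the studies shows difference in mean", and gives an SD range of 0.55 to 0.68.

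Power also has a role in the outcome hierarchy. Under Outcome and assessments the authors write that "we will limit our secondary outcomes to outcomes with at least" 80 % power, with all other outcomes treated as exploratory. The Discussion counts power above 80 % for every secondary outcome among the strengths of the design.

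**The concern.** A power figure should follow from the difference, alpha, group size and test given beside it. The yes/no row does not, and the gap is too large for rounding or for the choice between common versions of the chi-squared test.

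The row matters more than its place in the table suggests. Table 5 is the only support shown for the rule that secondary outcomes have at least 80 % power, and this row is the one printed closest to that limit. A reader who checks it cannot tell whether the rates, the group size, the test or the power is the wrong entry.

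**Working it through.** **Inputs.** Group size 250 and alpha 0.0125 come from the sample size section and Table 5. Rates 0.50 and 0.34 come from the last row of the table. Sidedness is not stated. The null hypothesis, to "reject the null hypothesis that the population means of the experimental and control groups are equal", suggests a two-sided test, and the rows below reproduce only on that basis.

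**Step 1: reproduce what can be reproduced.** For a two-sample t test with n per group, the noncentrality is (δ/σ)·√(n/2), with √(250/2) = 11.18. The two-sided critical value at alpha 0.0125 with 498 degrees of freedom is about 2.507.

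| Row | δ/σ | Noncentrality | Power computed | Power printed |
|---|---|---|---|---|
| Primary, 150 h, SD 500 | 0.300 | 3.35 | 0.801 | 80 % |
| Days to first employment or education | 1.511 | 16.9 | 1.000 | 1.000 |
| Cognition | 0.429 | 4.79 | 0.989 | 0.989 |
| PSP | 0.500 | 5.59 | 0.999 | 0.999 |
| Self-efficacy | 0.329 | 3.68 | 0.880 | 0.880 |

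This supports 250 per group and a two-sided alpha of 0.0125 as the basis of the table.

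**Step 2: the yes/no row.** With pooled variance under the null, power = Φ{[|p1 − p2| − z·SE0] / SE1}, where:

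- z = 2.498 (two-sided 0.0125)
- mean rate = (0.50 + 0.34)/2 = 0.42
- SE0 = √(2 × 0.42 × 0.58 / 250) = 0.04414
- SE1 = √[(0.50 × 0.50 + 0.34 × 0.66) / 250] = 0.04356
- power = Φ[(0.16 − 2.498 × 0.04414) / 0.04356] = Φ(1.142) = **0.873**

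The continuity correction subtracts ½ × (1/250 + 1/250) = 0.004 from the difference. Power is then Φ[(0.156 − 0.1103) / 0.04356] = Φ(1.050) = **0.853**.

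**Step 3: other versions of the test and other inputs.**

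- Same inputs, other methods: unpooled 0.880; arcsine 0.874; noncentral chi-squared 0.870; exact enumeration of Pearson's test 0.875; exact enumeration of the corrected test and of Fisher's test 0.855.
- Other inputs: one-sided 0.920; 236 per group 0.850 (0.827 corrected); alpha 0.0167 gives 0.894; both IPS arms combined against control, 2:1, about 0.956.

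None gives 0.807. The nearest, 236 per group with correction, is 2.0 points away and departs from the stated 250.

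**Step 4: what would give 0.807.**

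- With the printed rates and alpha, about 214 per group: Φ[(0.16 − 2.498 × 0.04771) / 0.04708] = Φ(0.867) = 0.807. With correction, about 227 per group.
- With 250 per group and the printed rates, alpha of about 0.0056.
- With 250 per group, alpha 0.0125 and 50 % in the other arm, a control rate between 35 % (0.817) and 35.5 % (0.785). With correction, it lies between 34.5 % (0.824) and 35 % (0.792).

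The documents state none of these for this row.

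**Step 5: self-esteem.** δ/σ = 0.3/0.55 = 0.545 gives noncentrality 6.10 and power 0.9998, which would print as 1.000. δ/σ = 0.3/0.68 = 0.441 gives 4.93 and power 0.992, the printed value.

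**The case against.** The strongest reply is that nothing depends on the error. The printed power is lower than the inputs give, so the table errs on the cautious side. The sample size rests on the primary outcome (150 h, SD 500), which reproduces. If the rates are right, power is 0.873; if the printed power is right, it is 0.807. Either way the outcome meets the 80 % rule, and the claim in the Discussion still holds. All of this stands, and it limits the point to a correction of the table.

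A reader might go further and infer that the calculation used a higher control rate, so that this outcome falls short of 80 % and should be exploratory. The documents do not support that. They give no control rate other than 34 %, and a calculation that fell short would have printed a figure below 0.80. For the outcome to miss the limit, both the printed rates and the printed power would have to be wrong.

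It could also be said that an unstated method explains 0.807. Two routes come within 2 points: halving alpha again to 0.00625 (0.817), and a three-group test with 2 degrees of freedom and an assumed middle rate of 42 % (0.794). Neither is stated for the row, and neither gives 0.807. The 1.25 % level is already the result of dividing for four comparisons.

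On self-esteem, the row's own note discloses the SD range, and 0.992 is the power at its cautious end. That is fair: the gap is 0.8 points, far from any threshold, and the entry is a labelling slip.

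**Conclusion.** The point holds as an arithmetic inconsistency with a small consequence. For 50 % vs 34 %, 250 per group and two-sided alpha 0.0125, the power is 0.873, not 0.807: a difference of 6.6 points, or 4.6 to 4.8 points if a continuity-corrected or Fisher test is meant. This rests on the group size given in the text and on two-sided testing, which is inferred from the rows that reproduce. The documents do not show which cell of the row is wrong.

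The design does not change. The error understates power, the outcome keeps its secondary status on the printed figures, and the sample size is unaffected. The self-esteem row is a side remark: its SD column appears to show one end of the disclosed range while its power column uses the other.

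**What to change.** Reconcile the yes/no row of Table 5 in one of two ways:

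- If 50 % vs 34 % is what was intended, print 0.87, or 0.85 with a note that a continuity-corrected or Fisher test is meant.
- If 0.807 is what was intended, state the rates, the group size and the test variant that produced it, and confirm that power is at least 80 %.

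In the self-esteem row, print SD 0.68 with 0.992, or SD 0.55 with power above 0.999.

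The cost is two table cells and at most a footnote. No analysis, sample size or outcome definition has to change.
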